### Temporal and between-hospital variation in outcomes (RQ3)

We will assess the variation over time and between hospitals on all primary and secondary outcome measures. Risk-adjustment will be based on logistic regression or other regression models, as appropriate for each outcome measure. Both patient-level and operation-level predictors will be included, such as age, gender, operation type and the constituent variables of previously published and validated risk adjustment models such as the Portsmouth Physiological and Operative Score for the enumeration of morbidity and mortality (P-POSSUM) and the Surgical Outcome Risk Tool (SORT) (Prytherch et al. 1998; Protopapa et al. 2014).

### Association between outcomes and hospital structures and processes of care (RQ4)

To describe the relationship between outcomes and hospital structures and processes, we will use mixed-effects models, employing random coefficients to assess the variation between hospitals. Patient-level covariates will be included as appropriate to distinguish the effect of case-mix from the effect of hospital characteristics on outcomes.

### Relationship between different postoperative outcomes (RQ5)

We will evaluate the association between different outcome measures which purport to assess similar constructs (e.g. short-term morbidity) and between outcomes which may be associated with each other. As an example for the latter, the relationship between short-term complications and long-term survival has been demonstrated previously (Moonesinghe et al. 2014; Khuri et al. 2005; Toner and Hamilton 2013); however, there are fewer data evaluating the relationship between a complicated postoperative course and health-related quality of life or disability free survival. We will use odds ratios, Pearson correlations and statistical measures of agreement as appropriate.

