## Introduction

Approximately 1.5 million major surgical procedures are carried out in the UK National Health Service per year at a cost of around £5 billion (Abbott et al. 2017); globally, surgical caseload substantially exceeds 300 million procedures per annum (Weiser et al. 2015). International estimates of death within 30 days of planned (elective or expedited) surgery vary, but it is acknowledged to be relatively uncommon in high income nations (around 0.6% to 4% depending on the study design, health system and population characteristics) (Abbott et al. 2017; Pearse et al. 2012; Ghaferi et al. 2009). However, there are several reasons why these low estimates of short-term mortality may provide false reassurance about the quality of perioperative care and the potential health and economic burden on patients and society. First, the incidence of major or prolonged postoperative morbidity is at least ten times higher than short-term mortality (Moonesinghe et al. 2014). This is important, because major morbidity contributes to increased length of hospital stay and associated increased cost of healthcare. Second, US data have shown wide variation in risk-adjusted morbidity and failure-to-rescue rates between the sample of healthcare providers who voluntarily participate in the American College of Surgeons’ National Surgical Quality Improvement Program (ACS-NSQIP), suggesting that at least some of these poor short-term outcomes could be avoidable (Ghaferi et al. 2009; Ghaferi et al. 2009). However, the lack of a unified national system for measuring complications across different types of major surgery in the NHS means that it is currently not possible to ascertain if the UK has the same problem. Third, a consistent finding across different procedures, populations and healthcare systems is the independent association between short-term postoperative complications and reduced longer-term survival (Moonesinghe et al. 2014; Khuri et al. 2005; Toner and Hamilton 2013). It therefore follows, that the outcome of surgery should not be defined entirely by short-term survivorship. Longer-term and additional patient-centred outcomes such as quality of life or disability-free survival are increasingly viewed as important measures of perioperative ‘success’ by both clinicians and patients, but there is comparatively little high quality data on these outcomes (Boney et al. 2016; Myles et al. 2016). This is particularly important given the evolving demographics of the surgical population (increasing age and multi-morbidity) and the increased number of surgical options available for previously untreatable conditions. There is also a recognition that not all interventions are in the best interests of patients, and sometimes less invasive approaches may lead to better outcomes and fewer adverse events (Skou et al. 2015; Kise et al. 2016). Thus, understanding the full implications of a surgical intervention is critical to supporting high quality patient care and shared decision making.

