### Research questions

What is the level of compliance with evidence-based structures and processes for patients undergoing major surgery?What are the rates of complications, failure to rescue (FTR), short- and long- term mortality in patients undergoing major planned surgery in NHS hospitals?How do the rates of adverse outcomes vary over time and between institutions?Are there structural or process related predictors of these adverse outcomes?What is the relationship between different measures of postoperative outcomes (e.g. different measures of morbidity; short and longer-term outcomes, health-related quality of life and disability)?What is the validity and predictive performance of previously published risk prediction models for different perioperative outcomes in the PQIP population?Can existing risk models be improved, or more parsimonious versions developed to support temporally responsive risk adjustment and clinically useful risk evaluation?How representative is the sample of patients recruited to PQIP of the total cohort of patients undergoing potentially eligible procedures in PQIP hospitals?Is there an outcome benefit to hospital and/or patient involvement in PQIP which can be differentiated from secular variation?Can quality of care be improved through a theoretically underpinned complex intervention supporting the use of data for improvement at local level, and do patient outcomes also improve?

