### Dataset

The dataset has been informed using the best available evidence. The primary outcome is the presence of any POMS-defined morbidity on postoperative day seven. Secondary outcomes will include: POMS-defined major morbidity (Wong et al. 2017); complications graded according to the Clavien-Dindo classification; failure to rescue (FTR); resource utilisation (critical care admission (planned/unplanned); critical care length of stay, hospital length of stay, hospital readmission within 30 days of index procedure); mortality at 90 days; days alive and out of hospital (Moonesinghe et al. 2017)censored at 30 days, 60 days, 90 days and one year postoperatively; disability-free survival at one year; change in patient reported health related quality of life (HRQOL) between baseline and 6 and 12 months after surgery; the responses to the “Ask2Questions” brief questionnaire about complex pain (Faculty of Pain Medicine, London, UK 2022). The choice of outcome measures has been based on formal validation studies (Grocott et al. 2007; Dawson et al. 2001; Shulman et al. 2015)and expert consensus (Clavien et al. 2009; Hutchings et al. 2012; Hutchings et al. 2013; Hutchings et al. 2014; Neuburger et al. 2011; Neuburger et al. 2012; Neuburger et al. 2013; Neuburger et al. 2013). To calculate FTR, we will follow previously described methodology, but using the presence of a Clavien-Dindo grade II or above complication as our definition of postoperative complications (Silber et al. 1992; Silber et al. 2007). Given the changes in how perioperative care is coordinated (e.g. enhanced recovery programmes aiming for early discharge) we will also use different endpoints for mortality to compare and contrast different approaches to how FTR could be measured in the modern era – for example, inpatient death vs. 30-day mortality vs. 60-day mortality). Candidate variables for risk adjustment have been selected from the results of a systematic review, and subsequent original research (Moonesinghe et al. 2013; Protopapa et al. 2014; Canet et al. 2010). These include: physiological measurements (e.g. blood pressure); long-term conditions and their control (e.g. diabetes and HbA1C and heart failure / New Your Heart Association grade) and laboratory results (e.g. haematological and biochemistry assays), as well as more novel measures such as deprivation index. Process measures have been informed by systematic review (Chazapis et al. 2018) and Delphi consensus process. An expert panel (the Clinical Reference Group) of stakeholders from different medical and surgical specialties provided further input to refine the long-list of potential measures. These include measures of staffing (level of seniority of surgeons and anaesthetists involved in care delivery), intraoperative anaesthesia and surgical practice, and enhanced recovery metrics before and after surgery. In addition to prospectively collected data, we will also link patient-level data with NHS Digital Hospital Episode Statistics and the Office of National Statistics mortality register. We will also consider patient-level linkage with other registries such as the National Cancer Registry, the Intensive Care National Audit and Research Centre’s Case-Mix Programme and relevant National Clinical Audits, in order to provide a comprehensive dataset at lowest local data collection burden.

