
#### Study flow

Patients are approached for participation either by mail, at the preoperative assessment clinic or on the day of surgery. A minimum of 1 h is allowed for patients to consider the information on the participant information sheet before they are asked whether they wish to consent. At the time of consent, patients are asked to indicate whether they wish their longer-term follow-up to be by email or telephone. Following consent, the patient is asked to complete baseline demographic and HRQOL data. On the day of surgery, clinical teams or research staff complete preoperative, intraoperative and recovery room data. Further objective data capture occurs on day 2 or 3 (the Drinking Eating and Mobilising process measure (Levy et al. 2016)), day 7 (the Post-Operative Morbidity Survey (POMS) (Grocott et al. 2007)) and at hospital discharge (the Clavien-Dindo complications grading scale (Clavien et al. 2009; Dindo et al. 2004), and information about the length of stay and post-discharge destination of the patient. In addition, patients are asked to complete a patient satisfaction with anaesthesia questionnaire (Bauer et al. 2001; Walker et al. 2016)within 24 h of surgery, a quality of recovery questionnaire at baseline (at the time of consenting to participate in PQIP) and postoperative day 3 (Stark et al. 2013; Chazapis et al. 2016), and longer-term HRQOL and disability-assessment questionnaires at baseline, 6 and 12 months after surgery (Dawson et al. 2001; Shulman et al. 2015).

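### RQ5 states no case-mix adjustment for relating complications to later survival, disability and quality of life; used as named, its statistics would mix complications with preoperative risk

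*Protocol article*

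**What the plan says.** In the protocol article's list of research questions, RQ5 asks "What is the relationship between different measures of postoperative outcomes", with examples that include short- against longer-term outcomes, quality of life and disability. The analysis section for RQ5 splits this into two tasks. One compares measures of the same construct, such as short-term morbidity. The other relates outcomes that may be linked, with complications and long-term survival as the example. It then points to the gap the study could fill: "there are fewer data evaluating the relationship between a complicated postoperative course and health-related quality of life or disability free survival". The methods for both tasks are given in one sentence: "We will use odds ratios, Pearson correlations and statistical measures of agreement as appropriate".

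Four other places bear on this:
- The Introduction describes the existing evidence as "the independent association between short-term postoperative complications and reduced longer-term survival".
- The RQ3 section says "Risk-adjustment will be based on logistic regression or other regression models, as appropriate for each outcome measure" and lists predictors. The RQ4 section plans mixed-effects models with patient-level covariates to separate case-mix from hospital characteristics.
- The Dataset section lists candidate preoperative variables for risk adjustment and includes among the secondary outcomes "change in patient reported health related quality of life (HRQOL) between baseline and 6 and 12 months after surgery".
- Study flow has patients complete "longer-term HRQOL and disability-assessment questionnaires at baseline, 6 and 12 months after surgery", so baseline scores are available.

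**The concern.** Patients in poorer condition before surgery can be expected to have both more complications and worse outcomes a year later. A crude odds ratio or a Pearson correlation between the two therefore contains whatever the shared preoperative risk contributes. The Introduction motivates the question with an independent association, which is an adjusted quantity, yet the RQ5 section names no tool that is adjusted by construction.

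This matters most for HRQOL and disability-free survival, where the article itself says evidence is thinner and where the study would add most. With a recruitment target of 70,000, an interval around a crude estimate could be narrow and still centred away from the adjusted association.

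The concern does not reach the first task in RQ5. Agreement statistics are the right tool for comparing POMS with Clavien-Dindo, and adjustment is not needed there.

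**Working it through.** **Text comparison.** The article states no figure for RQ5, so there is nothing to reproduce. What can be compared is the level of detail:

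| Section | Model named | Case-mix covariates named |
|---|---|---|
| RQ3 | Logistic or other regression | Yes, with examples |
| RQ4 | Mixed-effects models | Yes, patient level |
| RQ5 | None | No |

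The descriptive-statistics section promises unadjusted and adjusted outcomes, but labels that RQ2. The article therefore does mention adjustment at this level of summary, and RQ5 is where it is absent.

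**Size, model A (all inputs assumed).** Let z be a standard normal preoperative risk score.
- logit P(complication) = −1.5 + b·z
- logit P(poor later outcome) = −1.3 + b·z + log(OR)·complication

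At z = 0 these give a complication risk of 18% and, without a complication, a poor-outcome risk of 21%. Here b is the log-odds per SD of risk for both outcomes: b = 0.2 is an odds ratio of e^0.2 = 1.22 per SD, and b = 1.0 is e^1.0 = 2.72. Averaging over z by numerical integration gives the crude 2×2 table, and crude OR = (n11·n00)/(n10·n01).

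Example with b = 0.5 and conditional OR 1.0. The cell proportions are 0.0502 (both), 0.1435 (complication only), 0.1753 (poor outcome only) and 0.6310 (neither). Crude OR = (0.0502 × 0.6310)/(0.1435 × 0.1753) = 1.26.

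| b | Crude OR, conditional OR 1.0 | Crude OR, conditional OR 1.5 |
|---|---|---|
| 0.2 | 1.04 | 1.56 |
| 0.3 | 1.09 | 1.63 |
| 0.5 | 1.26 | 1.85 |
| 0.8 | 1.69 | 2.42 |
| 1.0 | 2.09 | 2.95 |

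The 1.0 column is the cleaner one. In the 1.5 column the crude and conditional odds ratios would differ somewhat even without confounding, because odds ratios do not collapse over covariates.

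**Size, model B (all inputs assumed).** A single binary risk factor is present in 20% or 40% of patients. In low-risk patients the complication risk is 12% and the death risk 3%. The factor has the same odds ratio with both outcomes.

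Example with 20% high risk, factor OR 3 and conditional OR 1.0:
- High-risk complication risk: odds 0.12/0.88 × 3 = 0.409, risk 0.290. High-risk death risk: odds 0.03/0.97 × 3 = 0.0928, risk 0.0849.
- Complication and death: 0.8 × 0.12 × 0.03 + 0.2 × 0.290 × 0.0849 = 0.00781. Complication and alive: 0.14625.
- No complication and death: 0.8 × 0.88 × 0.03 + 0.2 × 0.710 × 0.0849 = 0.03317. No complication and alive: 0.81277.
- Crude OR = (0.00781 × 0.81277)/(0.14625 × 0.03317) = 1.31.

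Over the two prevalences, with conditional OR 1.0, the crude OR is 1.03–1.04 (factor OR 1.5), 1.11–1.12 (OR 2), 1.31–1.32 (OR 3) and 1.71–1.78 (OR 5). With conditional OR 1.5 it runs from 1.55 to 2.63.

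Both models point the same way: negligible distortion when shared risk is weak, material when it is strong.

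**Baseline score.** With equal variances and baseline-to-follow-up correlation r (assumed), the variance of a change score relative to a baseline-adjusted analysis is 2(1 − r)/(1 − r²) = 2/(1 + r). That is 1.43 at r = 0.4, 1.33 at r = 0.5 and 1.18 at r = 0.7. This is a secondary point about efficiency, separate from confounding.

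**The case against.** The strongest reply is that silence is not a decision. An odds ratio is the usual output of an adjusted logistic model, the method sentence carries a qualifier about appropriateness, and a condensed article may leave covariates to a fuller protocol or analysis plan. This stands in part: it would be wrong to say the plan excludes adjustment. It does not remove the point, because the sentence is a choice of tools, and the same article names adjustment in the neighbouring sections.

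A reader might also infer that the study intends to report these associations as effects of complications. The documents do not support that. The research question and the RQ5 section speak of relationship and association throughout, and the reference to independence in the Introduction describes earlier literature.

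Three further replies have force:
- RQ3 and RQ4 concern hospital comparison, where case-mix adjustment is integral, so the contrast with RQ5 is suggestive only. Unadjusted statistics are legitimate for comparing measures of one construct.
- Pearson correlation is not assigned to any particular pair of variables, so the text does not show it being applied to binary or graded outcomes.
- The magnitudes rest wholly on assumed inputs and on an analysis that is in fact crude. Weak shared risk makes the distortion trivial.

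Listing change in HRQOL as an outcome does not rule out a baseline covariate either, and efficiency is a minor matter at the planned sample size.

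**Conclusion.** The point holds for the second task of RQ5 only. For relating complications to later survival, disability-free survival and HRQOL, the article names no adjusted method. Followed as named, it would give associations that mix the complication with preoperative risk.

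With no conditional association, model A gives a crude odds ratio of 1.04–1.09 for weak shared risk (b = 0.2–0.3) and 1.26–2.09 for moderate to strong shared risk (b = 0.5–1.0). Model B gives 1.03–1.78. These are illustrations on assumed inputs; the documents do not say where in the range the study lies.

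The plan neither commits to unadjusted analysis nor claims a causal effect, and neither should be read into it. What is open to criticism is that a better method, feasible with data already collected, is not named where it is needed.

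**What to change.** Split the RQ5 method statement in two.

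1. For measures of the same construct (POMS against Clavien-Dindo), keep agreement statistics.
2. For complications against later outcomes, use regression adjusted for the preoperative risk variables and operation type, with a hospital effect. For 6- and 12-month HRQOL and disability, model the follow-up score with its baseline value as a covariate. Report crude and adjusted estimates side by side, and label the crude ones descriptive.

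The cost is a change of wording and a little more analysis work, with no new data collection. Two refinements are optional and the point does not depend on them: a Cox model for survival from a landmark after complications have been assessed, and the same baseline covariate where HRQOL change is compared under RQ3.

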### Evaluation of existing risk prediction models (RQ 6)

We will evaluate discrimination (using the area under receiver-operator-characteristics curves) and calibration (using Hosmer–Lemeshow or Pearson correlation statistics) of known risk prediction models including the P-POSSUM, SORT and Surgical Risk Scale.

### Developing new models for the prediction of risk (RQ 7)

We will develop and internally validate new models for the prediction of risk, using logistic or other regression models as appropriate. Penalised regression models will be considered to reduce the risk of overfitting. These analyses may lead to a modification of the dataset with the aim of reducing data collection burden, if we find parsimonious models that are able to do without some variables previously considered important for risk prediction.

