#### Sample size

Target recruitment is 70,000 patients. It is expected that this will take at least 5 years to achieve. The long observation period will facilitate the study of how data collection and feedback impacts upon patient outcomes over time.

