## Discussion

PQIP has now been running for 4 years, and was paused for approximately one year during the Covid pandemic, both because elective surgery activity reduced substantially, and because clinical and research teams were diverted to support the emergency response. Review of data collected to that point and discussion with clinical teams has found that the random sampling approach was largely infeasible at hospital level. Therefore, a convenience sampling approach has been adopted by most sites. This further underlines the importance of our planned analyses to evaluate risk of bias in our patient selection and our results.

This also highlighted another challenge with our approach: the direct cost of participation in the study. Hospitals are incentivised to take part because the PQIP patient study is registered on the National Institute for Health Research’s portfolio of approved studies: therefore, sites are financially rewarded for recruiting patients. However, the costs of data collection and entry must be covered locally, and this is a significant challenge, which has limited both site participation and the number of patients recruited per site. Nonetheless, over 126 hospitals have taken part in the PQIP patient study so far, and over 35,000 patients have been recruited.

PQIP has also successfully collaborated with another research team to facilitate an NIHR funded randomised controlled trial to use the PQIP data collection platform and co-recruit into both studies (https://www.journalslibrary.nihr.ac.uk/programmes/hta/NIHR130573/#/) This approach to efficient trial design should bring benefit to patients, clinicians, researchers and provide excellent value for money.

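### Internal validation of the new risk models should be joined by a temporal validation, because pooled checks would not show calibration drift over time

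*Protocol article*

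**What the plan says.** The section on developing new models (RQ 7) states the check in one sentence: "We will develop and internally validate new models for the prediction of risk, using logistic or other regression models as appropriate". The next sentence names the threat: "Penalised regression models will be considered to reduce the risk of overfitting". The section adds that the modelling may lead to variables being removed from data collection. It names no resampling scheme, and no other section describes testing the new models on a later period. The RQ 6 section evaluates published models in PQIP data, which does not validate the new ones.

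The Objectives call for models that are updated regularly and serve case-mix adjustment and risk prediction for different outcomes. The Research questions want models that "support temporally responsive risk adjustment and clinically useful risk evaluation".

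On the data, the Sample size section says "Target recruitment is 70,000 patients" and "It is expected that this will take at least 5 years to achieve". The Discussion reports that "over 126 hospitals have taken part in the PQIP patient study so far, and over 35,000 patients have been recruited", that "PQIP has now been running for 4 years, and was paused for approximately one year during the Covid pandemic", and that "a convenience sampling approach has been adopted by most sites".

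**The concern.** The named check and the named threat do not match the stated use. Overfitting is a problem of too few events for the number of parameters. A model that must follow change over time faces a second problem: baseline risk or predictor effects may differ between the period of fitting and the period of use. The article itself reports a break, a pause of about a year after which elective practice and case selection may have changed.

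Bootstrap or random-fold validation draws its fitting and test patients from the same mixture of periods. A good result then says little about patients treated later. At stake is the expected risk against which sites would be compared if the models are used for feedback. Drift in the model could then read as better or worse care. The modelling may also cause variables to be dropped, and items no longer collected prospectively are hard to recover.

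**Working it through.** The plan gives no performance target to reproduce, and 70,000 is stated without a derivation, so it is used here only as an input.

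**Inputs from the article.** 35,000 patients so far and a target of 70,000; 126 hospitals; 30-day mortality of 0.6% to 4% (Introduction, international estimates). **Assumed, because not given.** POMS morbidity 10% to 30%; 20, 50 or 100 candidate parameters; model R² at 15% of its maximum; the size of between-hospital variation and of drift.

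**1. Expected optimism.** The uniform shrinkage S solves n = p / [(S − 1) ln(1 − R²/S)], with p the number of parameters and R² = 0.15 × R²max. For event rate φ, R²max = 1 − exp{2[φ ln φ + (1 − φ) ln(1 − φ)]}.

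- φ = 10%: R²max = 0.478, R² = 0.0717. With p = 50 and S = 0.9812: 50 / (0.0188 × 0.0759) ≈ 35,000.
- φ = 0.6%: R²max = 0.0707, R² = 0.0106. With p = 50 and S = 0.882: 50 / (0.118 × 0.0121) ≈ 35,000.

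| Event rate | N | Events | S, 20 par. | S, 50 par. | S, 100 par. |
|---|---|---|---|---|---|
| 10% | 35,000 | 3,500 | 0.992 | 0.981 | 0.963 |
| 30% | 35,000 | 10,500 | 0.995 | 0.987 | 0.975 |
| 10% | 70,000 | 7,000 | 0.996 | 0.990 | 0.981 |
| 30% | 70,000 | 21,000 | 0.997 | 0.994 | 0.987 |
| 4% | 35,000 | 1,400 | 0.987 | 0.968 | 0.939 |
| 0.6% | 35,000 | 210 | 0.949 | 0.882 | 0.789 |
| 0.6% | 70,000 | 420 | 0.974 | 0.937 | 0.882 |

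Optimism is at most about 4% for the common outcome. For mortality at 0.6% it runs from about 3% to 21%.

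A simulation (126 hospitals × 278 patients, 50 parameters, assumed between-hospital SD 0.4) agrees. With 21.6% events, AUC was 0.732 apparent and 0.729 by random 10-fold cross-validation. With 0.62% events (217), AUC fell from 0.795 to 0.749, with slope 0.80.

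**2. Drift over time.** A logistic model with an intercept, checked on random folds, gives a pooled O/E of about 1 whatever the drift, because each fold has the same mix of periods as the fitting data. In simulation with an assumed post-pause change:

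- Pooled random cross-validation: O/E 1.00, slope 0.98.
- Fit pre-pause, test post-pause, intercept shifted by −0.25 logit: O/E 0.86.
- Fit pre-pause, test post-pause, predictor effects multiplied by 0.75: slope 0.76.

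A hand check of the shift at a uniform risk of 20%: odds 0.25 × exp(−0.25) = 0.25 × 0.779 = 0.195, so risk 0.163 and O/E 0.163/0.20 = 0.81. This is of the same order as the simulated 0.86, which averages over patients of differing risk and includes chance.

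**3. Hospitals.** With an assumed between-hospital SD of 0.3, about 11% events and 40 parameters, the 10th to 90th percentile of hospital O/E was 0.63 to 1.38 from random folds and 0.63 to 1.39 with whole hospitals held out. With 126 hospitals, leaving a few out hardly moves the fit.

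Events per hospital now: 35,000/126 = 278 patients, so 28 to 83 morbidity events at 10% to 30%, but 278 × 0.006 = 1.7 to 278 × 0.04 = 11 deaths.

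**The case against.** The strongest reply is that the article does not exclude the check asked for. It names no resampling scheme, and validation that holds out hospitals or periods within the development data can be called internal. Such detail is commonly left to a full protocol or analysis plan, and neither is shown. This stands: a reader might infer that nothing but random resampling is planned, and the text does not support that.

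A reader might also infer that internal validation is almost uninformative at this sample size. That fails for rare outcomes. The models are for different outcomes, mortality among them, and at 0.6% both internal validation and penalisation do real work.

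A third tempting reading is that ordinary cross-validation hides differences between hospitals. Step 3 shows otherwise for differences in baseline risk, since random-fold predictions tabulated by hospital show the same spread. That spread is also partly the quality signal that RQ3 sets out to measure, so it is not model failure in itself. The simulation had equal-sized hospitals and varied only the intercept. It says nothing about predictor effects that differ by hospital.

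Finally, the plan partly deals with time and selection already: models are to be updated regularly, RQ3 examines variation over time, and the sample is to be compared with HES. Updating answers drift once it is seen, but does not show whether the version in use fits the current period. Some change in O/E over time may be real improvement, which RQ3 and RQ9 measure. This argues for reviewing temporal results with judgement, not against obtaining them.

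**Conclusion.** The point holds as a recommendation about the choice of analysis, not as an error in the document. For the common primary outcome, the threat that the plan names is small (shrinkage about 0.96 to 0.997), and pooled internal validation would not show the threat that its own temporal aim raises. Under modest assumed drift the difference is material: O/E 0.86 or slope 0.76 on later patients, against 1.00 and 0.98 in the pooled check.

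The shrinkage range rests on the assumed event rate, parameter count and R². The drift figures illustrate what could be missed; they are not estimates of what happened after the pause. Internal validation should stay, above all for rare outcomes. The documents do not support calling it useless, nor treating between-hospital O/E spread as a fault of the model.

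**What to change.** Keep internal validation and penalisation. In the RQ 7 section, add a temporal validation: fit on pre-pause (or earlier) patients, test on post-pause (or later) patients, and report calibration-in-the-large, calibration slope and c-statistic. Also report calibration slope and discrimination by hospital or group of hospitals, grouped for rare outcomes. Review the temporal results before a model is used for feedback or to drop variables from the dataset. Do not make feedback conditional on the between-hospital O/E spread.

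No new data collection is needed, but it is not free. It takes some extra analysis and reporting, the reported performance will look slightly less favourable, and hospital-level estimates for rare outcomes will be imprecise at about 1.7 to 11 deaths per hospital. Any change to the dataset between periods would complicate the split. The check does not cure bias from consent or convenience sampling, since the later patients are selected in the same ways.
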